### 2.7 Computerized Cognitive Remediation Therapy

This study will employ the CCRT system (Nanjing Weisi Medical Technology Co., 
Ltd., model VCRT-G, Nanjing, Jiangsu, China) from the Rehabilitation Medicine 
Department of the Second Affiliated Hospital of Xinxiang Medical University. 
Patients will receive training under the guidance of trained professional 
therapists. The hardware architecture of the CCRT system comprises a single 
server and multiple treatment terminals, while the software architecture is 
divided into three components: the frontend, backend, and an extensive database. 
The frontend is integrated with multiple therapy terminals. Upon accessing a 
terminal, therapists are presented with all available training tasks, enabling 
patients to engage directly in cognitive training activities. The backend 
functions as the central host, primarily utilized for entering general patient 
information, selecting and initiating tasks, and monitoring and reviewing task 
completion status. The database is responsible for storing all patient-related 
therapy data, thereby facilitating statistical analyses by researchers. The CCRT 
includes 6 therapeutic modules: executive function, learning and memory, 
attention, perceptual-motor skills, language, and social cognition. Treatment is 
administered sequentially through these modules in a progressive manner. During 
each session, patients undertake multiple therapeutic tasks derived from various 
exercises, with each exercise offering multiple levels of difficulty.

The CCRT system encompasses over 10 distinct therapeutic tasks. Below are 
several examples: (1) Emotion Recognition: Patients observe facial expressions in 
presented images and select the corresponding emotional label. Correct choices 
earn points, enhancing social cognition; (2) Voice Coach: Patients listen to 
audio prompts and drag the described image into a collection box. Higher accuracy 
and quantity improve scores, targeting language comprehension; (3) Whack-a-Mole: 
Patients quickly tap moles randomly appearing from holes. Faster responses yield 
higher scores, training rapid decision-making; (4) Supermarket Shopping: A 
simulated store scenario where patients follow a shopping list to locate items 
across sections, integrating executive function training; (5) Train Arrival: 
Patients adjust track switches to guide color-matched trains to correct stations, 
refining attentional control; (6) Task Cards: Patients identify and drag cards 
matching textual instructions into a collector, boosting pattern recognition; (7) 
Memory Master: Patients memorize sequentially displayed items and recall them 
under time constraints, strengthening memory retention. The system automatically 
adjusts the current training difficulty based on indicators such as the patient’s 
accuracy rate and response time from previous cognitive training stages, thereby 
adapting to improvements in the patient’s cognitive functions. CCRT is 
administered once daily, 5 times per week, over a period of 4 weeks, culminating 
in a total of 20 sessions. Relevant studies indicate that the concurrent 
application of tDCS with cognitive training enhances task accuracy more 
effectively than when these therapies are conducted separately [43]. 
Consequently, it has been determined that in Group 1 (HD-tDCS + CCRT) will be 
administered simultaneously rather than sequentially.

### 2.8 Blood Sampling and Analysis

After a 8-hour fast, 5 mL of blood will be collected into an EDTA-K_2_ 
anticoagulant tube. Post-centrifugation at 3000 rpm for 10 minutes, two distinct 
polyethylene tubes will be used to separate the supernatant from the sedimented 
blood cells. The supernatant and sedimented blood cells will be separated into 
two distinct polyethylene tubes. The protein concentration in the supernatant 
will be determined using the BCA kit (Qingdao Jieshikang Biotechnology 
Co., Ltd., Cat# RYX148, Qingdao, Shandong, China). Subsequently, protein samples 
and protein molecular weight markers in equal volumes will undergo Tris-sodium 
dodecyl sulfate polyacrylamide gel electrophoresis. The gel will be moved onto a 
polyvinylidene fluoride membrane and blocked with a 5% skim milk solution for 
two hours. Following washing, primary antibodies against BDNF, GDNF, and 
β-actin (dilution 1:500) will be added and incubated overnight at 4 
°C. The antibodies used were as follows: anti-BDNF (Cat# 28205-1-AP, 
Proteintech Group, Inc., Wuhan, Hubei, China); anti-GDNF (Cat# 26179-1-AP, 
Proteintech Group, Inc.); and anti-β-actin (Cat# 66009-1-Ig, Proteintech 
Group, Inc.). The horseradish peroxidase (HRP)-conjugated secondary antibodies to 
be used are as follows: anti-rabbit IgG (for BDNF and GDNF detection; Cat# 
SA00001-2, Proteintech Group, Inc.) and anti-mouse IgG (for β-actin 
detection; Cat# SA00001-1, Proteintech Group, Inc.). Specific lot numbers will 
be recorded upon procurement. Then, these secondary antibodies will be added at a 
dilution of 1:5000 and incubated at room temperature for two hours. The PVDF 
membrane (Cat# E801, Vazyme, Nanjing, Jiangsu, China) containing the target 
proteins will be placed in a chemiluminescent developer, with the exposure time 
adjusted according to protein abundance. Quantitative analysis of BDNF and GDNF 
expression will be conducted using ImageJ software (version 1.53t, National 
Institutes of Health, Bethesda, MD, USA). Each assay parameter will be measured 
in duplicate for all samples. The identities of all subjects will be coded by the 
investigator until the completion of all biochemical analyses. Fig. 3 provides a 
comprehensive overview of the trial’s timeline, assessment schedule, and 
arrangements.

**Fig. 3. S3.F3:**
[figure not shown]
**Schematic representation of the randomized controlled trial**. The experimental timeline, assessment schedule, and grouping arrangements. (A) 
Introduces the sequence of interventions as well as the timing and content of 
assessments. (B) Details how intervention sessions will be administered by week. 
ARS, adverse reaction scale; BDNF, brain-derived neurotrophic factor; BPRS, Brief 
Psychiatric Rating Scale; CGI, Clinical Global Impressions; fMRI, functional 
magnetic resonance imaging; GDNF, glial cell line-derived neurotrophic factor; 
GIQ, General Information Questionnaire; PANSS, Positive and Negative Syndrome 
Scale; SDSS, Social Dysfunction Screening Scale; SQLS, Schizophrenia Quality of 
Life Scale.

### 2.9 Outcome

The primary outcome measure used in this research is the MATRICS Consensus 
Cognitive Battery (MCCB), which is a crucial tool for assessing cognitive 
deficits in schizophrenia. It evaluates seven distinct cognitive domains: working 
memory, abstract thinking, attention/vigilance, processing speed, visual 
learning, verbal/visual learning, reasoning and problem-solving. The battery 
comprises the following subtests: (1) Trail Making Test A (TMT-A), (2) Symbol 
Coding, (3) Hopkins Verbal Learning Test-Revised (HVLT-R), (4) Digit Span Test 
(DST), (5) Stroop Color-Word Test, (6) Spatial Span Test (derived from the 
Wechsler Memory Scale III, WMS-III), (7) Verbal Fluency Test (VFT), (8) Mazes, 
(9) Brief Visuospatial Memory Test-Revised (BVMT-R), and (10) Continuous 
Performance Test-Identical Pairs (CPT-IP).

Secondary outcome measures include the Brief Psychiatric Rating Scale (BPRS), 
the PANSS, the Clinical Global Impression 
(CGI) scale, the Social Disability Screening Schedule (SDSS), the Schizophrenia 
Quality of Life Scale (SQLS), and fMRI. Specifically, the general information 
questionnaire is utilized to collect basic information about the patients. BPRS 
primarily assesses the severity of psychotic symptoms, with total scores ranging 
from 18 to 126, where higher scores reflect more severe symptoms. PANSS is used 
to evaluate the presence and severity of various symptoms. CGI scale is applied 
to assess the patient’s overall condition and therapeutic efficacy. SDSS measures 
the extent of social functional deficits. SQLS is designed to evaluate the 
quality of life in schizophrenia. For detailed information, please see Table 2.

**Table 2. S3.T2:** **Schedule of enrollment, interventions, assessments, and visits 
of patients**.

	Recruitment	Baseline	Assessments		
			Weekend 2	Weekend 4	6-month follow-up
Time point		T0	T1	T2	T3
Prescreening for eligibility, consenting and clinical interview					
Recruitment					
Eligibility screening	√				
Informed consent	√				
Allocation	√				
Primary outcome assessment					
MCCB		√	√	√	√
Second outcome assessment					
BPRS		√	√	√	√
PANSS		√	√	√	√
CGI		√	√	√	√
SDSS		√	√	√	√
SQLS		√	√	√	√
GIQ		√			
MRI		√	√	√	√
Blood sample collection (BDNF and GDNF levels)		√		√	√
Safety					
ARS			√	√	

A checkmark (√) indicates the time point at which each assessment is 
carried out. MRI, magnetic resonance imaging.

### 2.10 Data Collection and Management

The assessment and examination related to the study scales will be conducted by 
clinical physicians who are external to the experiment and remain blinded to the 
study content. Outcome data collection will be managed by dedicated personnel, 
also external to the experiment, and will be systematically recorded in 
electronic Case Report Forms (CRFs). To ensure patient confidentiality, patient 
identification numbers will be utilized during data entry. The collected data 
will be transferred to a secure database for storage. After all data collection 
is completed, specialized analysts will conduct. Access to the data will be 
restricted exclusively to the principal investigator, data collectors, and 
analysts, and no modifications or exports will be permitted without 
justification. As patients will undergo follow-up and re-evaluation six months 
post therapy, they will be contacted and reminded via telephone, email, social 
media, and other communication methods at the appropriate time. During this 
period, no one except the principal investigator, data collectors, and analysts 
will be allowed to access, view, modify, or export the data without cause. Since 
patients will be followed up and re-evaluated six months after the ends, we will 
contact and remind them via phone calls, emails, social media, and other means at 
that time. During the data collection phase, participants who report significant 
changes in their antipsychotic medication regimen within the 6-month follow-up 
period will be identified and documented. Data from these participants will be 
included in all analyses up to the T2 time point, but will be excluded from the 
primary analysis of the T3 (6-month follow-up) data to prevent confounding the 
primary study outcomes.

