### 2.4 Blinding

Throughout the study period, both participants and evaluating psychiatrists 
remained blinded. In implementing blinding procedures, we will adhere to these 
considerations and measures. The specific group assignments of patients will be 
disclosed only to the principal investigator. Patients were unaware of the 
details of allocation sequences and were explicitly instructed not to discuss 
with each other any aspects of group allocation, received therapies, 
questionnaire completion, or other experimental procedures. Participants will 
keep unaware of the allocation sequences and will be explicitly instructed not to 
discuss any aspects of group allocation, receive therapies, questionnaire 
completion, or other experimental procedures. To minimize potential interference 
with blinding by therapy personnel, we will employ four distinct therapy groups, 
each responsible for implementing their respective therapies. Each group was 
informed only of their own protocol and had no knowledge of group allocation 
details or the therapy plans of other groups. Communication between groups 
regarding specific therapy content will be strictly prohibited. During the 
experimental phase, the principal investigator will provide each group with the 
specific protocol for their corresponding group, after which each group will 
implement the therapies for their assigned patients. During the outcome 
measurement phase, personnel responsible for data collection and analysis will 
keep blinded to group allocation and specific therapy. The principal investigator 
implemented a “two-stage unblinding” procedure. Once the data was locked, the 
initial unblinding was conducted, dividing the data into Groups 1–4 without 
disclosing their actual relationships or true assignments. The unblinding will be 
conducted after the data analysis is completed, clearly indicating the specific 
group representations of 1–4.

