### 2.13 Harms

To examine the safety of HD-tDCS and track any adverse reactions participants 
might experience, an adverse reaction scale will be employed. An adverse reaction 
assessment form specific to HD-tDCS was developed for this study, encompassing 
common adverse reactions such as headache, skin tingling, fatigue, itching, 
burning sensations, and local discomfort. The design of this scale facilitates 
the prompt identification and management of any issues that may arise during the 
process. In the event of a serious adverse reaction, the current therapy will be 
discontinued, appropriate health evaluations will be conducted, and the incident 
will be communicated to the ethics committee. All adverse events will be 
systematically recorded in the CRF with respect to their incidence, types, and 
severity. The final study results will include a comprehensive summary of adverse 
events for each study group (Groups 1–4), including the frequency, severity, and 
percentage of participants affected by each type of adverse event. This will 
enable safety comparisons across the different interventions. To mitigate 
potential adverse reactions associated with the study, professional therapists 
will be engaged to implement the therapy, and they will receive comprehensive 
training pertinent to the study.

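### The HD-tDCS-specific adverse reaction scale is not excepted from the blinded raters' tasks, so without sham its answers can hint at who was stimulated and put assessor blinding at risk

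*Protocol article*

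**What the plan says.** On who rates, section 2.10 of the protocol article begins with a general rule: "The assessment and examination related to the study scales will be conducted by". The people it then names come from outside the trial team; they are "clinical physicians who are external to the experiment and remain blinded to the" subject matter of the trial. No scale is excepted. Section 2.4 makes a matching promise: "Throughout the study period, both participants and evaluating psychiatrists" are to stay unaware of allocation. For outcomes it adds that in the "measurement phase, personnel responsible for data collection and analysis will" likewise not know group or therapy.

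On the ARS, section 2.13 says that an "assessment form specific to HD-tDCS was developed for this study, encompassing" a set of listed reactions. The list is introduced as "common adverse reactions such as headache, skin tingling, fatigue, itching"; it also includes burning and discomfort at the site. One purpose given for the form is "the prompt identification and management of any issues that may arise during the" course of treatment. For harms, the final report is to present "events for each study group (Groups 1–4), including the frequency, severity, and" share of patients affected. The same section calls the form a scale, and Table 1 lists the ARS among the key secondary outcomes.

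On timing, Table 2 ticks the ARS at T1 and T2. MCCB, BPRS, PANSS, CGI, SDSS and SQLS are ticked at T0, T1, T2 and T3.

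On sham, Group 4 has no HD-tDCS or CCRT sessions (section 2.1), Group 3 has CCRT only, and the Discussion acknowledges that sham controls are lacking.

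**The concern.** The trial is described as double-blind, but without sham a patient knows whether electrodes were applied. Blinding of the efficacy raters is therefore the main protection left for scales that rest on rater judgement. A form about sensations under the electrodes, put by the same physician at the same visit, can tell that physician which patients were stimulated.

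PANSS, BPRS, CGI and SDSS are the most exposed. This matters more because Table 1 lists PANSS and BPRS as primary outcomes, while section 2.9 lists them as secondary. The MCCB consists of performance tests and leaves less room for rater expectation.

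There is a related risk at the analysis stage. Section 2.4 has the data analysed as coded Groups 1–4 before the codes are identified. An HD-tDCS-specific form tabulated by coded group could show which two codes were stimulated.

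**Working it through.** The plan gives no figure for this point, so the check is a reading of the text followed by an illustration.

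**Step 1: does the text place the ARS with the blinded raters?** Section 2.10 covers the study scales without exception. By the article's own labels (section 2.13, Table 1) the ARS is a study scale. No section names who administers it, sets the order within a visit, or separates it from the efficacy ratings. A literal reading includes the ARS, but this is an inference from a general sentence.

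**Step 2: what can the answers show?** Headache and fatigue are non-specific. Tingling, itching, burning and local discomfort point towards stimulation, and no sham arm masks the contrast. At most the answers separate Groups 1 and 2 (24 patients) from Groups 3 and 4 (24 patients). They do not identify the four arms.

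**Step 3: how informative could they be?** Let s be the proportion of stimulated patients, and c the proportion of unstimulated patients, who report such a sensation. Both are assumptions; the documents give neither. Suppose a rater calls every reporter stimulated and everyone else unstimulated. With equal halves:

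- correct guesses = 0.5 × s + 0.5 × (1 − c)
- share of reporters who were stimulated = s / (s + c)

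| s | c | Correct guesses | Reporters who were stimulated |
|---|---|---|---|
| 0.20 | 0.15 | 0.10 + 0.425 = 0.525 | 0.20/0.35 = 0.57 |
| 0.40 | 0.05 | 0.20 + 0.475 = 0.675 | 0.40/0.45 = 0.89 |
| 0.50 | 0.05 | 0.25 + 0.475 = 0.725 | 0.50/0.55 = 0.91 |
| 0.70 | 0.00 | 0.35 + 0.50 = 0.85 | 1.00 |
| 0.80 | 0.05 | 0.40 + 0.475 = 0.875 | 0.80/0.85 = 0.94 |

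The range is about 53% to 88% correct, against 50% by chance.

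**Step 4: which comparisons would be affected?** Suppose the rater shifts the score of each reporting patient by b. The mean shift is then b·s in Groups 1 and 2 and b·c in Groups 3 and 4.

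- Interaction (G1 − G2 − G3 + G4): b·s − b·s − b·c + b·c = 0.
- Group 1 versus Group 2: b·s − b·s = 0.
- Group 1 versus Group 3: b·(s − c).
- HD-tDCS main effect, the mean of G1 and G2 minus the mean of G3 and G4: b·(s − c).

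Over the rows above, s − c runs from 0.05 (0.20 − 0.15) to 0.75 (0.80 − 0.05). The cancellation needs the same b throughout and equal reporting rates in the two stimulated groups and in the two unstimulated groups.

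**The case against.** The strongest reply is that the article never says who completes the ARS. Table 2 places it under a separate safety heading. Its stated monitoring purpose, together with the trained therapists mentioned in section 2.13, fits completion by therapists. A condensed article may also leave the administrator and the order within a visit to the full protocol. This stands as far as it goes: that the raters will in fact administer the ARS is not established. It does not remove the point, because section 2.10 states a general rule that takes in the ARS and no section carves it out.

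A reader might infer that the ARS reveals the allocation, undoes assessor blinding at every post-baseline visit and biases the trial towards its hypothesis. The documents do not support that:

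- T1 ratings are affected only if the ARS comes before them, and no order is set.
- Carry-over to T2 or T3 needs the same rater to see the same patient again, which is not stated. The ARS is not scheduled at T3.
- Only stimulation status can leak, and only with some probability.
- A uniform shift cancels in the HD-tDCS × CCRT interaction, which section 2.11 uses to test synergy, and in Group 1 versus Group 2.

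Section 2.10 also limits data access to the principal investigator, data collectors and analysts. The rating physicians are not listed, so part of the separation exists already. It does not cover answers given to a rater in person, and it leaves the ARS open to analysts.

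A last objection is that Group 4 has no treatment sessions and so nobody to complete the form. Section 2.4 provides four therapy teams, one per group, which answers this.

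**Conclusion.** The point holds as a risk to assessor blinding, not as a demonstrated loss of it. Following section 2.10 literally would expose the efficacy raters, at T1 and T2, to answers that are informative about stimulation. The outcomes mainly at risk are PANSS, BPRS, CGI and SDSS; the comparisons are Group 1 versus Group 3 and the HD-tDCS main effect. The interaction, Group 1 versus Group 2 and the MCCB are less exposed.

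The size cannot be fixed from the documents. The 53% to 88% range rests entirely on assumed reporting rates and a simple guessing rule, so the leak could be slight or large. The cancellation in the interaction rests on a uniform rater shift. The point merits correction because the gap is specific and cheap to close.

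**What to change.** In section 2.10 and Table 2, except the ARS from the blinded raters' tasks. Have it completed in the same way in all four groups by each group's own therapy team (section 2.4). At minimum, someone other than the efficacy rater should complete it. State that the efficacy scales are always completed by a rater who has not seen the patient's ARS answers. Keep ARS entries closed to raters throughout, and to analysts until the blinded efficacy analysis is complete. The safety summary by group can follow.

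The cost is a few sentences and an access setting in the electronic case report form. Group 4's team will need a set contact at T1 and T2, because that group has no sessions. The small downside is that safety forms are filled in by unblinded staff, so adverse-event ascertainment may differ between groups. Using the same form, questions and time points in every group limits this.

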### 2.11 Statistical Analysis Plan

The sample size was calculated using G*Power software (version 3.1.9.7, 
Heinrich-Heine-Universität Düsseldorf, Düsseldorf, Germany), 
employing an F-test and a repeated-measures ANOVA model. In this study, we 
established the probability of a Type I error (α) at 0.05, the 
probability of a Type II error (β) at 0.20, and the statistical power (1 
- β) at 0.80, with an effect size (f) of 0.25. The required sample size 
was calculated to be 36 participants. Accounting for a 20% dropout rate and 
ensuring equal group sizes, the target sample size was determined to be 48 
participants, with 12 participants per group. The calculation of the sample size 
mentioned above is based on the sample size calculation methods adopted in 
previous literature [50]. An article suggests that when designing a preliminary 
study with no prior information for reference, a sample size of 12 participants 
per group is appropriate based on feasibility, improvements in the precision of 
mean and variance estimates, and regulatory considerations [51]. The 
sample size in this study satisfies the previously mentioned criteria and will 
offer enough statistical power to achieve the objectives.

We will utilize histograms and the Shapiro-Wilk test to assess the normality of 
the data distribution. For normal distribution data, continuous variables will be 
reported as mean ± standard deviation, whereas categorical data will be 
presented as frequencies (n) and percentages (%). Statistical tests such as 
one-way analysis of variance (ANOVA), Mann-Whitney U test, *t*-test, and chi-square 
test will be employed to assess baseline differences among groups. In accordance 
with the Consolidated Standards of Reporting Trials (CONSORT) guidelines, all 
analyses will be conducted using the intention-to-treat (ITT) principle, whereby 
participants will be analyzed according to their original randomization group. To 
address missing data within the ITT framework, we will employ linear 
mixed-effects models. These models are appropriate for making valid inferences 
under the missing-at-random assumption and are well-suited for managing the 
unbalanced data resulting from participant drop-out. To specifically assess the 
synergistic effect between HD-tDCS and CCRT, the models will incorporate the 
HD-tDCS × CCRT interaction as a fixed effect. We will conduct 
sensitivity analyses by comparing the results derived from mixed-effects models 
to evaluate the robustness of our findings. Line charts will be employed to 
visualize the data, offering a clear depiction of outcome value trends across 
time points. Given the repeated-measures nature of the data, we will utilize 
statistical methods suitable for this design. In addition to the mixed-effects 
models, we will explore non-parametric repeated-measures approaches where 
applicable. These methods are suitable for analyzing between-group differences at 
specific time points and changes within groups over time for both primary and 
secondary outcomes. Moreover, the Likelihood Ratio Test will be used to 
specifically assess the effect of the therapy. The Bonferroni correction will be 
employed to adjust *p*-values, addressing the issue of multiple comparisons from 
evaluations at different time points.

To further elucidate the underlying mechanisms, we will conduct correlation 
analyses to investigate the relationships between alterations in neuroimaging 
metrics, serum levels of BDNF/GDNF, and cognitive performance scores in 
participants. Additionally, we intend to utilize mediation analysis models to 
assess whether intervention-induced changes in brain activity and/or BDNF/GDNF 
levels mediate improvements in cognitive outcomes. Moreover, we will perform an 
exploratory analysis of the CCRT metrics (e.g., task accuracy, reaction time) to 
compare cognitive performance during training between the HD-tDCS + CCRT group 
(Group 1) and the CCRT group (Group 3). This analysis could clarify the immediate 
neuroenhancing potential of concurrent HD-tDCS.

A stable antipsychotic medication regimen will be required for all patients, 
requiring consistent dosing for a minimum of two weeks prior to the trial and 
maintaining this regimen unchanged throughout the study period. This protocol 
will be implemented to minimize confounding effects on clinical outcomes, in 
accordance with recommendations from previous literature [52]. The Defined Daily 
Dose (DDD) methodology will be utilized to standardize antipsychotic medication 
doses across study groups. This involves converting administered doses into DDD 
units following randomization to ensure pharmacological equivalence. To account 
for dosing variability and maintain the accuracy of results, DDD values will be 
incorporated as a covariate in all statistical models. All collected data will be 
entered into a database and analyzed using SPSS version 20.0 (IBM Corp., Chicago, IL, USA). Significance is 
defined as *p *
< 0.05.

